**Figure 1 f1:**
[figure not shown]
Overview of the Study Design

### Assessments and Instruments

Three measurement points will be considered (Table 1). Considering the context of data gathering, care has been taken to avoid overburdening participants with excessive questionnaires. The screening will include sociodemographic data and RAG. The first assessment, before the first session, includes some additional sociodemographics, PG13-R, HADS, Brief COPE, ECR-RS, AAQ-II, and MSPSS. The second assessment will include PG13-R, HADS and the working alliance measure (WAI-S). The follow-up assessment period (3rd assessment) will occur six months after the last assessment. These will include all outcomes (PG13-R, HADS, PTGI). The interventions will share the same assessment periods and instruments. The follow-up assessment ensures that all participants are evaluated one year after the death, enabling a PGD diagnosis.

**Table 1 t1:** Time Points for Measurement

Instrument	Screening	T1	T2	6 mths
Sociodemographics	x	x		
Risk Assessment for Grief (RAG)	x			
PG-13-R		x	x	x
The Hospital Anxiety and Depression Scale (HADS)		x	x	x
The Posttraumatic Growth Inventory (PTGI)				x
Brief COPE		x		
Experiences in Close Relationships (ECR-RS)		x		
Acceptance and Action Questionnaire II (AAQ-II)		x		
The Multidimensional Scale of Perceived Social Support (MSPSS)		x		
The Working Alliance Inventory-short form (WAI-S)			x	

*Note*. T1 = Pre-treatment; T2 = 12 weeks/Post-treatment; 6 months = follow up.

Participants will be contacted sensitively to inquire about the reasons for discontinuing the intervention. Clinical teams will receive supervision for each intervention, and adherence to treatment measures will be monitored.

#### Screening

Sociodemographic data, such as participants' gender, age, marital status, education, employment, and mental health and treatment history, are also collected.

##### Risk Assessment for Grief (RAG)

RAG is a hetero-assessment scale of PGD risk developed by the New Zealand Ministry of Health (Ministry of Health, 2017) and adapted for the DGS norm 003/2019 (DGS, 2019). It includes four items (anger, accusation/guilt, current relationships and general coping with grief) evaluated on a 5-point Likert scale. This instrument classifies the degree of PGD risk as low (<7 points), moderate (7-10 points) and high (≥ 10 points).

#### Primary Outcome

##### Prolonged Grief Scale – Revised (PG13-R)

The PG13-R is a self-report scale developed by Prigerson and colleagues (Prigerson et al., 2021) based on DSM-5-TR criteria for PGD. PG-13-R includes 13 items, evaluated on a 5-point Likert scale. PG-13-R grief symptoms represent a unidimensional construct with high degrees of internal consistency in research conducted at Yale (Cronbach's α = .83), Utrecht (Cronbach's α = .90), and Oxford (Cronbach's α = .93) universities. PGD diagnosis is attributed when the person obtains a total value greater than 30 and meets the temporal (12 months) and impairment criteria.

#### Secondary Outcome

##### The Hospital Anxiety and Depression Scale (HADS)

The HADS, originally developed for individuals with somatic diseases in hospitals (Zigmond & Snaith, 1983), measures anxiety and depression symptoms. The scale was developed for non-psychiatric populations and includes 14 items evaluated on a 4-point (0-3) Likert scale. Values higher than eight in each subscale suggest clinically relevant symptomatology. In the Portuguese adaptation (Pais-Ribeiro et al., 2007), Cronbach alpha values were .76 in anxiety and .81 in depression.

#### Predictors and Other Relevant Variables

##### Posttraumatic Growth Inventory (PTGI)

The PTGI (Tedeschi & Calhoun, 1996) evaluates the extent of perceived positive transformations following a challenging event. Comprising 21 items, it encompasses five subscales: personal strengths, appreciation of life, new possibilities, spiritual changes, and relation to others. Participants were instructed to assess each item on a 6-point Likert scale, ranging from 1 to 6. The overall PTGI score represents the sum of all items and higher scores indicated higher levels of posttraumatic growth. The original version of the PTGI has shown excellent internal reliability (Cronbach's α = 0.90) and acceptable test-retest reliability (*r* = .71). The PTGI has also shown good psychometric properties in breast cancer Portuguese samples (Silva et al., 2009).

##### Brief COPE

The Brief COPE (Carver, 1997) is composed of 28 items organized into 14 coping strategies. Each coping strategy is measured using two items (humour, positive reframing, emotional and social support, acceptance, religion, instrumental support, planning, active coping, behavioural disengagement, self-blaming, substance use, venting, self-distraction, and denial). Participants were asked to answer each item with a Likert-type response scale ranging from 0 (I never do this) to 3 (I always do this). Mean scores were calculated for each coping factor. The study of internal consistency for each factor using Cronbach's alpha shows adequate values (in general α ≤ .60), taking into account there are only two items per factor for the original (Carver, 1997) and the Portuguese version (Ribeiro & Rodrigues, 2004).

##### Experiences in Close Relationships (ECR-RS)

The ECR-RS (Fraley et al., 2011) is a self-report instrument that measures adult attachment to relevant persons – in this case, the deceased – rated on a seven-point Likert scale that ranges from 1 (strongly disagree) to 7 (strongly agree). Its nine items are grouped into two dimensions: attachment-related anxiety (Items 1-6) and avoidance (Items 7-9). The total subscale score consists of the mean of the items and ranges from 1 to 7, with higher scores indicating higher attachment avoidance or anxiety. The Portuguese version showed adequate reliability (α ranged from .72 to .91) and construct validity (Moreira et al., 2015).

##### Acceptance and Action Questionnaire II (AAQ-II)

The AAQ (Bond et al., 2011) is a 7-item questionnaire with a single-factor structure measuring acceptance, experiential avoidance, and psychological inflexibility. In the Portuguese validation (Pinto-Gouveia et al., 2012), results from a Confirmatory Factor Analysis showed the goodness of fit of the model, and this version also demonstrated an excellent level of internal consistency (α = .90) and good convergent and discriminant validity. Individuals are asked to rate each statement on a 7-point Likert scale ranging from 1 (never true) to 7 (always true). This scale reflects the single domain of psychological inflexibility, with higher scores indicating greater psychological inflexibility.

##### The Multidimensional Scale of Perceived Social Support (MSPSS)

The MSPSS (Zimet et al., 1988) measures perceived social support from family, friends, and others. The 12 items are grouped into three factors (family, friends and significant others), each with four items, using a 7-point Likert scale (0 = strongly disagree, 7 = strongly agree). Examples of items include “There is a special person who is close by when I need him/her"; "I can talk about my problems with my family”. The Portuguese version of the MSPSS (Carvalho et al., 2011) demonstrated good psychometric qualities (α ranged from .85 and .95).

##### The Working Alliance Inventory-Short Form (WAI-S)

The WAI-S (Tracey & Kokotovic, 1989) is a widely studied 12-item self-report that measures how the client perceives the therapeutic alliance with the therapist, with a 7-point Likert scale ranging from 1 (never) to 7 (always). In addition to the overall alliance score, the WAI-S includes three specific subscales: bond, tasks, and goals (four items, respectively). Internal consistency for the Portuguese version is .89 for the patient version and .85 for the therapist version (Machado & Horvath, 1999).

### Statistical Analysis

To evaluate the impact of Empower-Grief relative to TAU on the primary outcome (prolonged grief symptoms) and secondary outcome (anxiety and depression), we will use a mixed-effects model. A mixed-effects model for longitudinal data (pre-post and a 6-month follow-up) accounts for the hierarchical structure of the data, with participants nested within treatment groups and the correlation between repeated measurements within subjects. The intention-to-treat principle will be followed in the analysis, ensuring that all participants randomized to each treatment condition are included in the analysis, regardless of whether they completed all assessments or adhered to the treatment protocol. To address missing data, multiple imputations will be employed, a statistical method that generates multiple plausible values for missing data points based on the observed data. This method preserves the relationships between variables and reduces the potential for bias due to missing data.

Before drawing inferences, a preliminary examination of model assumptions, including checks for the normality of residuals and homogeneity of variances, will be conducted. The primary outcome, prolonged grief severity, will be modelled using a linear mixed-effects model with fixed effects for treatment condition (Empower-Grief vs. TAU), time point (pre-treatment, post-treatment, and 6-month follow-up), and their interaction, and random effects for participants and treatment groups. Secondary outcomes, anxiety and depression symptoms, will be analyzed using similar mixed-effects models.

The sample size for this research project was estimated using G*Power software, employing a repeated measures analysis with a mixed-effects model. Assuming a low effect size of *d* = 0.25, a significance level of α = 0.05, and a power of 1-β = 0.80. With two treatment groups, Empower-Grief and treatment as usual, and measurements taken at three moments (baseline, post-treatment, and 6-month follow-up), the resulting estimated sample size for the study was 44 participants for both treatments, representing a robust size to detect the anticipated effect with high statistical power.

To assess the predictive value of the considered predictors (i.e., posttraumatic growth, coping, attachment to the deceased, psychological flexibility, social support, and therapeutic alliance) on treatment outcomes, separate regression analyses will be conducted for each outcome measure (prolonged grief, anxiety, and depression). For each outcome, we will fit a mixed-effects model with the baseline variable as a fixed effect, adjusting for treatment condition, time, and their interaction. The random effects’ structure will remain the same as in the primary analysis.

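### The primary model fits treatment arm as both a fixed and a random effect; the arm variance cannot be estimated, and under REML the standard errors of arm differences in level depend on it

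*Protocol article*

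**What the plan says.** The Statistical Analysis section of the protocol article describes a linear mixed-effects model for prolonged grief severity. It lists "fixed effects for treatment condition (Empower-Grief vs. TAU"), time point "and their interaction, and random effects for participants and treatment groups".

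The same section shows what it means by treatment groups. The sample-size paragraph begins "With two treatment groups, Empower-Grief and treatment as usual", so the groups are the randomised arms. The stated reason for a mixed model is that it "accounts for the hierarchical structure of the data, with participants nested within treatment groups".

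The structure is carried further. Anxiety and depression are to be analysed with similar models. For the predictor models, the random-effects "structure will remain the same as in the primary analysis".

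The section does not state whether estimation is by REML or maximum likelihood (ML), or which contrast tests the primary hypothesis.

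**The concern.** The two arms are the comparison of interest. They are not a sample from a population of arms. With two arms, the intercept and the fixed arm effect already use both group-level degrees of freedom, and nothing is left from which to estimate a between-arm variance. A model with both terms may give a singular fit, a zero variance, a convergence failure, or a variance that reflects starting values.

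Two things are at stake. First, an interval or p-value for a difference between arms in level, whether a treatment main effect or a contrast at post-treatment or six months, could rest on a number that the data do not determine. Second, even in the mildest case the analyst has to drop or alter a term of the primary model after seeing output, and that is discretion a prespecified analysis should not need.

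**Working it through.** **Inputs.** From the Statistical Analysis section: 44 participants, two arms, three visits, and the fixed and random terms listed above. Assumed, because the article does not give them: 22 per arm, total variance 1, within-person correlation 0.6, and a random intercept for arm with variance s²g. The article gives no standard error to reproduce. Its sample size of 44 is used here only as an input, and none of its stated inputs is an arm variance.

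**Why the variance is not identifiable.** REML uses only contrasts of the data that are free of the fixed effects. The arm indicators lie in the space spanned by the intercept and the fixed arm effect, so those contrasts contain no trace of the random arm intercept. The REML likelihood therefore cannot depend on s²g.

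**SE of an arm difference at one visit.** Each arm mean has variance 1/22 + s²g, so Var = 2 × 1/22 + 2 × s²g = 0.0909 + 2 × s²g.

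**SE of a treatment-by-time contrast.** A change between two visits has variance 2 × (1 − 0.6) = 0.8 per person, and the arm intercept cancels. Var = 2 × 0.8/22 = 0.0727, so SE = 0.27 whatever s²g is.

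| s²g (set by hand) | Var, arm difference at a visit | SE | SE, treatment-by-time | REML log-likelihood |
|---|---|---|---|---|
| 0 | 0.0909 | 0.30 | 0.27 | −41.640789 |
| 0.1 | 0.2909 | 0.54 | 0.27 | −41.640789 |
| 1 | 2.0909 | 1.45 | 0.27 | −41.640789 |
| 10 | 20.0909 | 4.48 | 0.27 | −41.640789 |

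The log-likelihood column comes from a numerical fit to the same set-up.

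**Second check, REML against ML.** One data set was simulated with 22 per arm, three visits, and between- and within-participant variances of 1. The two variances were re-estimated at each fixed s²g.

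- REML: the log-likelihood is −91.3294 at s²g = 0, 0.01, 0.1, 1, 10 and 100. The SE of the arm difference at baseline or six months is 0.388, 0.413, 0.592, 1.466, 4.489 and 14.147. The treatment-by-time SE stays at 0.400.
- ML: the log-likelihood is highest at s²g = 0 and falls steadily: −82.893, −83.088, −84.033, −85.990, −88.250, −90.548. The arm variance therefore goes to zero and the ordinary SE returns.

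**Predictor models.** A participant-level baseline predictor was added to the first set-up. Its coefficient (−0.1936) and SE (0.141) were the same at arm variances 0, 0.1, 1 and 10.

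**The case against.** The strongest case on the other side has five parts.

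- *The natural efficacy test is unaffected.* With treatment, time and their interaction in a repeated-measures design, the treatment-by-time term is the usual test, and its SE does not move. This stands for a random arm intercept. But the article names no primary contrast, so arm differences at a visit remain open to it. It also says random effects without restricting them to an intercept. A random arm-by-time term would make the interaction unidentifiable too.
- *The problem belongs to REML.* This stands: under ML, or with a zero-variance fit, the ordinary model is recovered. The article does not say which estimator will be used.
- *The predictor inferences survive.* This stands for the coefficients and SEs of participant-level predictors. The redundant term is still carried into those models and still affects their arm-level contrasts under REML.
- *The SE inflation is imposed.* This stands. The arm variances were set by hand, and nothing shows that a fit would return 0.1, 1 or 10. The roughly 15-fold range (4.48/0.30) shows that the SE is undetermined. It does not predict a result.
- *Describing participants as nested within arms is correct for a parallel-group trial.* This stands, and that description need not be removed.

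This is not a detail left to an unseen analysis plan, because the article states the structure explicitly.

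**Conclusion.** The primary model is wrong as written, with moderate severity. Treatment arm appears as both a fixed and a random effect, and the arm variance cannot be estimated separately from the fixed effect. Under REML the SE of any arm difference in level depends on an arbitrary variance: the usual sampling variance plus 2 × s²g. The figures assume 22 per arm, a correlation of 0.6 and total variance 1. The non-identifiability does not depend on these assumptions.

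A reader might infer that the trial's treatment comparison as a whole is undefined, or that the predictor analyses are invalid. The article does not support either reading. With a random arm intercept the treatment-by-time contrasts and the predictor coefficients are unaffected, and ML restores the usual SE. What remains is that the article, by naming neither estimator nor primary contrast, does not confine its inference to the unaffected terms.

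**What to change.** In the Statistical Analysis section, remove treatment groups from the list of random effects. Keep treatment, time and treatment-by-time as fixed effects, with a random effect for participants. Apply the same correction to the anxiety and depression models and to the predictor models. The description of participants as nested within arms may stay.

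If clustering by therapist was the intention, name therapist as the random factor. The Treatment Fidelity section lists four Empower-Grief and three TAU providers, but the model mentions none of them.

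The cost is one phrase. The article gives no arm variance among its sample-size inputs, so removing the term does not change the 44. It describes the trial as ongoing with analyses still planned, so on its own account the correction can be made before analysis.

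### Treatment arm is both a fixed effect and a two-level random effect; and, if the participant effect is an intercept only, the model imposes one common correlation on visits at about weeks 0, 12 and 38

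*Protocol article*

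**What the plan says.** The Statistical Analysis section of the protocol article specifies a linear mixed model for prolonged grief severity. Its fixed effects are treatment condition, "time point (pre-treatment, post-treatment, and 6-month follow-up), and their interaction". The random part is given as "and random effects for participants and treatment groups". The same section describes participants as nested within treatment groups and says that the model accounts for "the correlation between repeated measurements within subjects", without giving a form or a value for that correlation. The planned assumption checks include "checks for the normality of residuals and homogeneity of variances"; no check of the correlation pattern is named. Anxiety and depression get similar models, and the predictor models keep the random structure of the primary analysis.

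On timing, the note to Table 1 (Assessments and Instruments) reads "T2 = 12 weeks/Post-treatment; 6 months = follow up", and the text of that section says the third assessment "will occur six months after the last assessment". The visits therefore fall at about weeks 0, 12 and 38.

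**The concern.** The quoted random part raises two problems of different strength.

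1. **Arm as fixed and random (definite).** The sample-size paragraph uses the term treatment groups for the two arms, so the random term and the fixed treatment effect refer to the same two-level factor. A variance between arms cannot be learned from two arms whose means are already fitted freely. A standard error that carries this variance depends on whatever value the software happens to return.
2. **One common correlation (conditional).** A participant intercept with independent residuals gives every visit the same variance and every pair of visits the same correlation. Here the gaps are about 12, 26 and 38 weeks, and only the first contains the 12-week treatment period. If the true variances or correlations differ by visit, the model still applies one pooled variance to every change from baseline. The error rate of a 12-week or 6-month change contrast on the primary outcome then moves away from 5%. The named assumption checks would not detect unequal correlations.

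The same structure carries over to the secondary-outcome and predictor models.

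**Working it through.** The plan gives no figure for this point, so there is none to reproduce. The inputs from the document are 44 participants in total, two arms, three visits and alpha 0.05. The assumptions are 22 per arm (the allocation ratio is not stated), complete data, and the correlations and SDs below (the article gives neither).

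**Part 1: the random arm term.** Let g_E and g_T be random arm effects with variance σ_g².

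- The two arm indicators span the same space as the fixed intercept and fixed treatment effect. Degrees of freedom left for σ_g²: 2 arms − 2 fixed parameters = 0. The restricted likelihood does not depend on σ_g².
- The variance of the arm difference at one visit becomes 2σ_g² plus the sampling variance, so it contains a quantity that the data cannot supply.
- For a change from baseline, an arm intercept cancels: (g_E − g_T) − (g_E − g_T) = 0. The damage therefore falls on arm differences at a visit and on the treatment main effect, not on the change contrasts.

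**Part 2: the common correlation.** For visits j and k the within-person change variance is

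v_jk = s_j² + s_k² − 2·r_jk·s_j·s_k.

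The random-intercept model replaces each of these by the pooled value v = (v_12 + v_13 + v_23)/3. The ratio of model SE to true SE is √(v/v_12) for the 12-week change and √(v/v_13) for the 6-month change.

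Example with unit SDs and r12/r23/r13 = 0.7/0.7/0.5:
- v_12 = 2(1 − 0.7) = 0.6; v_23 = 0.6; v_13 = 2(1 − 0.5) = 1.0
- v = (0.6 + 0.6 + 1.0)/3 = 0.733
- 12 weeks: √(0.733/0.6) = 1.11; 6 months: √(0.733/1.0) = 0.86

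Type I error comes from 40,000 simulated null trials per pattern. The pooled test has 2 × 21 × 2 = 84 df and the contrast-specific test has 2 × 21 = 42 df.

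| r12/r23/r13 | v | v_12 | v_13 | SE ratio 12 wk | SE ratio 6 mo | Type I 12 wk | Type I 6 mo |
|---|---|---|---|---|---|---|---|
| 0.60/0.60/0.60 | 0.800 | 0.80 | 0.80 | 1.00 | 1.00 | 5.1% | 5.1% |
| 0.65/0.60/0.55 | 0.800 | 0.70 | 0.90 | 1.07 | 0.94 | 3.6% | 6.3% |
| 0.60/0.60/0.40 | 0.933 | 0.80 | 1.20 | 1.08 | 0.88 | 3.5% | 8.3% |
| 0.70/0.60/0.50 | 0.800 | 0.60 | 1.00 | 1.15 | 0.89 | 2.3% | 8.0% |
| 0.70/0.70/0.50 | 0.733 | 0.60 | 1.00 | 1.11 | 0.86 | 3.1% | 9.4% |
| 0.50/0.70/0.55 | 0.833 | 1.00 | 0.90 | 0.91 | 0.96 | 7.2% | 5.9% |
| 0.70/0.60/0.50, 12-week SD 1.3 | 1.000 | 0.87 | 1.00 | 1.07 | 1.00 | 3.6% | 5.0% |

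With exponential decay over weeks 0, 12 and 38 and r12 from 0.6 to 0.9, the SE ratios run from 1.25 to 1.40 at 12 weeks and from 0.88 to 0.83 at 6 months. Coverage of nominal 95% intervals is then 98.5 to 99.3% at 12 weeks and 91.8 to 89.6% at 6 months.

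Two comparisons bound the problem:
- A contrast-specific variance, which is what an unstructured covariance gives with complete data, holds type I error at about 5%, including when the correlations are truly equal.
- The joint 2-df arm-by-time test under the random-intercept model stays at about 5 to 6%. In the decay patterns the two opposite errors largely offset.

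**The case against.** The strongest objection is that the article never says intercept. It does not exclude slopes or a structured residual, and it says that within-subject correlation is handled. Covariance structure, degrees-of-freedom method and convergence fallback are ordinary content for a statistical analysis plan, which is not shown, so their absence is no fault. This stands, and it is why the second part is conditional. It does not touch the first part: the random arm term is written into the model and is wrong under any participant covariance.

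A reader might infer that the plan will make the 6-month interval too narrow and the 12-week interval too wide. The documents do not support that. It requires an intercept-only participant effect, correlation that fades with time, fairly stable variance, and inference on separate changes from baseline. The article fixes none of these. Equal correlations produce no error. Correlations of 0.50/0.70/0.55 make both intervals too narrow. A larger SD at 12 weeks can leave the 6-month test correct.

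The article also names no single-visit contrast, interval or primary time point. If inference rests on the joint interaction test, the distortion is small. For a plain arm difference at a visit with equal variances, the correlation pattern has no effect (SE ratio 1.00). Both points stand. The single-visit change contrasts are nevertheless the components of the planned interaction, and reporting them would be a natural next step.

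Finally, the trial calls itself exploratory. That lowers the stakes but does not make an unidentifiable term usable.

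**Conclusion.** The point holds in two parts.

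- **Definite:** treatment arm cannot be both a fixed effect and a two-level random effect. The random variance has zero degrees of freedom and is confounded with the treatment effect.
- **Conditional:** if the participant effect is an intercept with independent residuals, single-visit change contrasts are calibrated only when variances and correlations are equal across visits. Under the moderate fading illustrated by 0.65/0.60/0.55 and 0.7/0.7/0.5, type I error is about 6 to 9% at 6 months and 3 to 4% at 12 weeks. Stronger decay gives larger errors, and other patterns give none or a different direction.

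The sizes rest on assumed correlations, 22 per arm and complete data. The case for changing the covariance does not depend on which pattern is true: contrast-specific variance was calibrated in the patterns tried, and the common-correlation model was not. The change is worth making, with medium confidence about how much it will matter in this trial.

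**What to change.** Rewrite the model sentence in Statistical Analysis along these lines: treatment, time and their interaction enter as fixed effects only; the three measurements of a participant have an unstructured covariance; degrees of freedom are by Kenward-Roger; if the model does not converge, a participant random intercept is used as the prespecified fallback. Delete the random effect for treatment groups. Carry the same structure into the anxiety, depression and predictor models, which now refer back to the primary analysis.

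The cost is one sentence. An unstructured covariance over three visits has six parameters against two for a random intercept, so four more, which 44 participants can support. Degrees of freedom fall somewhat: in the complete-data calculation, from 84 to 42 for a change contrast. Removing the random arm term loses nothing, because the data hold no information about it.

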## Results

The RCT is ongoing. We have contacted 294 potential participants and recruited 44 to this moment. Recruitment will close in April 2024. We plan to complete data analyses by December 2024.

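### An effect of d = 0.25, 80% power and a total of 44 participants do not agree unless settings the article does not state are assumed

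*Protocol article*

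**What the plan says.** The sample-size paragraph of the protocol article (Method, Statistical Analysis) says that the size was "estimated using G*Power software, employing a repeated measures analysis with a mixed-effects model". The inputs are these:

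- Effect: "Assuming a low effect size of *d* = 0.25".
- Error rates: "a significance level of α = 0.05, and a power of 1-β = 0.80".
- Layout: two treatment groups, with "measurements taken at three moments (baseline, post-treatment, and 6-month follow-up".

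The conclusion drawn is that "the resulting estimated sample size for the study was 44 participants for both treatments, representing a robust size to detect the anticipated effect", and the sentence ends by calling the power high. The Abstract also gives forty-four as the number of participants, so 44 is the total and not the number per arm. The Results section reports "We have contacted 294 potential participants and recruited 44 to this moment".

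The primary model in the same section has fixed effects for treatment, time and their interaction. The article does not state which G*Power F test was used, the correlation between repeated measures, the sphericity correction, or whether d was converted to f.

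**The concern.** Cohen's d for two arms is the difference in means divided by the SD. A difference of 0.25 SD is small, and 22 per arm is far fewer than such a difference usually needs, even with repeated measures. G*Power's repeated-measures routines ask for f, and for two groups the usual conversion is f = d/2. Entering 0.25 as f would therefore size the trial for an effect twice as large as the one named.

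The stated power matters for interpretation. The comparator is supportive psychotherapy delivered by experienced therapists, so a modest difference between arms is realistic. The Background section sets out to evaluate effectiveness and hopes to influence national policy. A reader who trusts the power statement could take a non-significant result as evidence against a small benefit, although the trial would seldom detect one.

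**Working it through.** **Inputs from the article.** Effect 0.25 labelled d; alpha 0.05; power 0.80; k = 2 arms; m = 3 times; N = 44.

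**Assumptions, because no figure is given.** 1:1 allocation (22 per arm), two-sided or F test, no dropout, compound symmetry, and correlation rho between 0.3 and 0.8.

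**Step 1. Can the stated 44 be reproduced with G*Power's formulas?**

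- Interaction test: lambda = f² × N × m × eps / (1 − rho), with df = (k−1)(m−1)eps and (N−k)(m−1)eps.
- Between-factors test: lambda = f² × N × m / (1 + (m−1)rho), with df = k−1 and N−k.

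At rho = 0.5 and eps = 1, the total N for 80% power is:

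| Test | f = 0.25 | f = 0.125 (d = 0.25 converted) |
|---|---|---|
| Interaction | 28 | 106 |
| Between factors | 86 | 338 |

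None of these is 44. The settings found to give 44 at 80% power are:

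| f entered | Test | Other settings | Power at N = 44 |
|---|---|---|---|
| 0.125 | Interaction | rho 0.8, eps 1 | 0.813 |
| 0.25 | Interaction | rho 0.2, eps 1 | 0.813 |
| 0.25 | Interaction | rho 0.5, eps 0.5 | 0.801 |
| 0.25 | Between factors | rho 0 | 0.801 |

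The interaction test with f = 0.25, rho 0.5 and eps 1 also returns 44, but at 95% power (0.956) and not the stated 80%.

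**Step 2. What do these f values mean as a difference between arms?** Suppose the arms are equal at baseline and differ by d SD at both later visits. The differences over time are (0, d, d), with mean 2d/3. The interaction deviations in each arm are ±(−d/3, d/6, d/6). Their mean square is (d²/9 + d²/36 + d²/36)/3 = d²/18, so f = d/√18 = 0.236d.

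- f = 0.125 corresponds to d = 0.125 × √18 = 0.53 SD at both follow-ups.
- f = 0.25 corresponds to d = 0.25 × √18 = 1.06 SD at both follow-ups. Under the usual conversion d = 2f it is 0.5.

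**Step 3. Power for a 0.25 SD difference with 22 per arm.**

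- *One visit, two-sample t-test.* Noncentrality = 0.25 × √(22/2) = 0.829 on 42 df. Power is 12.8%.
- *2-df interaction, difference at both follow-ups.* lambda = (0.25²/18) × 44 × 3 / (1 − rho) = 0.458/(1 − rho), on 2 and 84 df.
- *Average of the two follow-ups, adjusted for baseline.* Variance factor v = (1 + rho)/2 − rho². Noncentrality = 0.829/√v.

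| rho | 2-df interaction | v | Baseline-adjusted average |
|---|---|---|---|
| 0.3 | 10% | 0.56 | 19% |
| 0.5 | 12% | 0.50 | 21% |
| 0.7 | 18% | 0.36 | 27% |
| 0.8 | 25% | 0.26 | 36% |

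At rho 0.9 the interaction test reaches 45%.

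**Step 4. Difference detectable with 80% power at N = 44**, from solving the Step 3 formulas for d:

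| rho | 2-df interaction | Baseline-adjusted average |
|---|---|---|
| 0.3 | 0.98 SD | 0.65 SD |
| 0.5 | 0.83 SD | 0.61 SD |
| 0.7 | 0.64 SD | 0.52 SD |
| 0.8 | 0.52 SD | 0.44 SD |

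For a t-test at one visit it is 0.86 SD.

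**The case against.** The strongest reply is that 44 can be obtained at the stated 80% power. One route keeps the printed effect: d = 0.25 converted to f = 0.125, with rho about 0.8. On G*Power's own metric, power at N = 44 with f = 0.125 is 31%, 41%, 63% and 81% at rho 0.3, 0.5, 0.7 and 0.8. This part stands: the printed inputs do not fix a unique N. It does not rescue the sentence, because interaction f = 0.125 in this layout is about a 0.53 SD difference at both follow-ups, roughly twice the effect named. The routes with f = 0.25 need the label d, or the description as low, to be wrong.

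A reader might go further and infer that the stated power is simply false and that the true figure is 10% to 25%. The document does not support that. The slip may lie in the effect-size label, in which case the calculation could be sound for a larger effect. The 10% to 25% range also belongs to one contrast only, the 2-df interaction with a constant effect after baseline.

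Three further points for the other side are fair. The trial calls itself exploratory, which can justify a small sample, though not a claim of high power for a small effect. An article may leave the routine, the correlation and the attrition allowance to the full protocol, so their absence is not the fault here. No passage says that a non-significant result will be read as lack of efficacy; that is a risk of interpretation and not a stated rule. The report of 44 recruited is no error either.

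**Conclusion.** The concern holds as an inconsistency among three printed figures. For a 0.25 SD difference between arms, 44 participants in total give about 10% to 36% power, depending on the contrast, for rho 0.3 to 0.8: 13% for a t-test at one visit, 10% to 25% for the 2-df interaction and 19% to 36% for the baseline-adjusted average. This assumes 1:1 allocation, compound symmetry, equal arms at baseline and no dropout; loss of participants would lower power. No ordinary correlation brings power for that difference close to 80%.

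A total of 44 at 80% power follows only from undeclared settings that imply a larger effect. Which of the label, the power or the sample size is wrong cannot be determined from the document. Either way, the description of the size as robust for the named effect is unsupported.

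**What to change.** Keep N = 44, which the Results section reports as already recruited, and change the text as follows.

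1. State the settings actually used: effect-size metric (d or f), G*Power test, correlation and sphericity setting. Then correct the effect size or the power so that the figures agree.
2. Name the primary contrast and report the difference detectable with 80% power for that contrast. Before attrition, and for rho from 0.8 down to 0.3, this is about 0.5 to 1.0 SD for the 2-df interaction, or about 0.45 to 0.65 SD for the baseline-adjusted average of the two follow-ups.
3. Delete the closing clause that calls the size robust and the power high.
4. Base conclusions on the estimate and 95% confidence interval of the same contrast, and do not read non-significance as lack of efficacy. Contrasts should not be mixed. At rho 0.5 the interval half-width is about 0.43 SD for the baseline-adjusted average, against about 0.61 SD for a single-visit comparison.

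The cost is wording only: no extra participants and no change to the analysis model. The one downside is that the stated figure becomes less favourable.
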